### Recruitment procedures

Active duty participants aged 18–50 years (inclusive) reporting acute, subacute, or chronic LBP who are able to provide voluntary written informed consent are eligible for this trial. Participants are ineligible if they have knowledge of a pending absence through the 6-week active treatment phase. Such absences could include a planned leave, deployment, temporary duty assignment, or permanent change of station. Participants unwilling to be allocated to either intervention arm are also ineligible. A detailed description of the inclusion/exclusion criteria is summarized in Table 1.

**Table 1 Tab1:** Eligibility criteria

Inclusion criteria	Rationale
Age ≥ 18 and ≤ 50	Age range of most active duty U.S. military personnel
Acute, subacute, or chronic low back pain	Low back pain commonly treated by primary care and chiropractic providers
Ability to provide voluntary written informed consent	Able to comprehend study details; able to make decisions without limitations or impairment
Active duty status at one of the three participating military treatment facilities	Chiropractic care available only to active duty personnel at U.S. military treatment facilities
Exclusion criteria	
LBP from a non-musculoskeletal source (pain from a visceral condition[s])	Care outside study scope needed; potential to confound health outcomes
Co-morbid pathology that may directly impact spinal pain	Care outside study scope needed; potential to confound health outcomes
Recent spinal fracture (within the last 8 weeks)	May influence ability to measure pain-related health outcomes; safety concern
Recent spinal surgery (within the last 12 weeks)	Potential to confound health outcomes due to natural history or from potential complications
Spinal or paraspinal tumor(s)	Care outside study scope needed
Spinal or paraspinal infection(s)	Care outside study scope needed
Spinal inflammatory arthropathy (rheumatoid arthritis, enteropathic spondyloarthropathy)	Potential to confound health outcomes
Contraindication(s) for spinal manipulation of the lumbar spine and pelvis (unstable spinal segments, cauda equina syndrome)	Care outside study scope needed
Pregnancy or plans to become pregnant within active treatment period	Potential to confound health outcomes
Diminished/altered mental capacity	May prohibit informed consent or compromise safety or compliance with study procedures

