#### Allocation

Participants remaining eligible after completing: 1) the consent process, 2) baseline interview, 3) clinical evaluation, and 4) baseline assessment are allocated to a treatment group. Allocation occurs within STaRS via an adaptive computer-generated minimization algorithm programmed to balance group assignment on the factors of sex (M, F), age (18 to <30, 30 to 50), LBP duration (<1 month, 1–3months, >3 months), and baseline Numeric Rating Scale (0–5, 6–10) measurement (worse pain in past 24 hours). Participants are allocated to one of two groups: 1) UMC or 2) UMC plus chiropractic care. PMs, participants, and all study personnel are unable to influence the group assignment, and future allocations are concealed.

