#### Primary outcome measures

The co-primary outcome measures are the Numeric Rating Scale (NRS) for average pain intensity during the past week and the Roland-Morris Disability Questionnaire (RMDQ). The NRS has excellent metric properties, is commonly used in RCTs studying LBP [34, 35], and has been demonstrated as a valid and reliable measure [36]. Participants are asked to rate their average level of LBP during the past week on an ordinal 11-box scale (0 = no LBP; 10 = worst possible LBP). The RMDQ is a reliable and valid LBP-related disability assessment instrument commonly used in clinical research [37, 38]. Containing 24 questions, it is considered sensitive to disability-related changes in patients with LBP [39–41].

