Secondary evaluations of the final models will compare group differences at week 12 to ascertain if the pattern seen at week 6 remains after the active care phase. Group differences will also be reported for week 2 and 4 to compare to the results of the pilot study. Secondary analyses will compare the percentage of patients with clinically meaningful improvement of at least 30 % relative to baseline at the week 6 endpoint on the co-primary outcome variables [49]. General estimating equations with a working covariance matrix will be used to estimate the differences in proportions between groups at each time point, with terms in the model for time (as a categorical variable), group, site, site-by-group, and time-by-group interactions, and the minimization variables. Consistent with the recent NIH Task Force recommendations [50] for a minimum dataset for chronic LBP, we will conduct an exploratory analysis over a range of improvement levels.

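### The 30% responder rule is undefined at a baseline of 0 and met by one point at baselines 1–3, and its model omits the baseline score of the scale analysed

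*Protocol article*

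**What the plan says.** The section Primary data analysis and sample size plans a secondary comparison of the percentage of participants whose improvement counts as clinically meaningful, set at 30% or more "relative to baseline at the week 6 endpoint on the co-primary outcome variables". It gives no minimum number of points and no rule for a baseline of 0. The differences in proportions are to come from estimating equations with terms for time, group, site, site-by-group, time-by-group and the minimization variables. A further analysis varies the threshold: "we will conduct an exploratory analysis over a range of improvement levels".

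On entry, Recruitment procedures says "A detailed description of the inclusion/exclusion criteria is summarized in Table 1". The only inclusion item in Table 1 about the back pain itself is "Acute, subacute, or chronic low back pain". No item in the table, inclusion or exclusion, sets a minimum on either scale.

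Under Primary outcome measures, average pain over the past week is scored "on an ordinal 11-box scale (0 = no LBP; 10 = worst possible LBP", and the RMDQ is described as "Containing 24 questions, it is considered sensitive to disability-related changes in patients with LBP". Under Allocation, the only severity variable among the minimization factors is "baseline Numeric Rating Scale (0–5, 6–10) measurement (worse pain in past 24 hours". This is a different NRS item from the co-primary one, and it is used in two categories.

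**The concern.** A percentage change from a person's own baseline is informative only if that baseline is large enough for the percentage to mean something. Nothing in Table 1 ensures this. A participant with intermittent pain could enter with a very low disability or past-week pain score, and the rule would then count the smallest possible movement on the scale as clinically meaningful.

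The model adds a second weakness. Responder status depends on where a participant starts, but the listed terms leave out the starting score on the scale being analysed. RMDQ is not a minimization factor either, so neither the allocation nor this model controls a chance imbalance in baseline RMDQ. The co-primary mixed models differ here: they include the baseline measurement as a modelled time point with equal group means.

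At stake is how the reported responder percentages are read, and some precision in comparing them. The main trial conclusion is not at stake.

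**Working it through.** **Inputs from the Protocol article.** Threshold 30% of own baseline. NRS in whole points from 0 to 10. RMDQ with 24 items, taken as 0 to 24 on the assumption of one point per item. SDs 5.4 (RMDQ) and 2.0 (NRS), given as pilot estimates for the sample size. The article states no responder rate or power for this analysis, so there is no figure to reproduce.

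**1. Smallest qualifying fall.** For baseline b, this is the smallest whole number k with k/b ≥ 0.30.

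| Baseline | Points needed | Fall as % of baseline |
|---|---|---|
| 0 | undefined (0/0) | – |
| 1 | 1 | 100 |
| 2 | 1 | 50 |
| 3 | 1 | 33.3 |
| 4 | 2 | 50 (one point is 25) |
| 6 | 2 | 33.3 |
| 10 | 3 | 30 |
| 14 | 5 | 35.7 |
| 24 (RMDQ only) | 8 | 33.3 |

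The one-point range is exactly 1 to 3 on both scales.

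**2. Baseline 0.** The outcome depends on coding. Written as a ratio, it is missing. Written as follow-up ≤ 0.7 × baseline, a participant who stays at 0 counts as a responder. The text is compatible with either.

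**3. Chance of meeting the rule with no true change.** P = 1 − Φ((k − 0.5)/s), where s is the assumed SD of random change; the 0.5 allows for rounding to whole points.
- s from 1.0 to 2.0: at baselines 1–3, 1 − Φ(0.5/1.0) = 31% to 1 − Φ(0.5/2.0) = 40%. At baselines 8–10 (k = 3), 1% to 11%.
- Measurement error of 1 to 2 points per occasion, so s = √2 × 1 = 1.41 to √2 × 2 = 2.83: 36% to 43% at baselines 1–3, 4% to 19% at 10, and 0% to 6% at 14.

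The values of s are assumptions; the documents give no measurement error. Under every value tried, the chance falls steeply from low to higher baselines.

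**4. Share of participants affected.** The documents do not give this. For illustration, take a beta-binomial shape with an assumed mean and the stated SD: p = mean/n, and variance = n·p·(1 − p)·[1 + (n − 1)ρ]. For RMDQ mean 8: p = 1/3, n·p·(1 − p) = 5.33, 5.4² / 5.33 = 5.47, ρ = 4.47/23 = 0.19.

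| Scale, assumed mean | At 0 | At 1–3 |
|---|---|---|
| RMDQ 8 | 4.7% | 20% |
| RMDQ 10 | 1.5% | 11% |
| RMDQ 12 | 0.5% | 5.5% |
| NRS 4 | 2.6% | 40% |
| NRS 5 | 0.7% | 23% |
| NRS 6 | 0.2% | 11% |

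**5. Model terms against what drives the outcome.** Steps 1 and 3 show that responder status depends on the baseline of the scale analysed. For the RMDQ, no listed term carries that information directly. For the NRS, the only related term is worst pain in the past 24 hours, split at 5/6, which puts baselines 1 and 5 in the same category and measures another item.

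**The case against.** The strongest case against is as follows.

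- **Zero coding.** How a derived variable treats a zero denominator is usually settled in an analysis plan, and that plan is not shown. This stands: the zero case alone would not be a finding. The relative threshold, the open entry criteria and the list of model terms are, however, stated in the article.
- **Intention-to-treat.** A reader might infer that zero-baseline participants will be silently dropped in breach of intention-to-treat. The documents do not support this. Statistical methods defines the approach as analysis by original allocation using all observed data, and step 2 shows that a missing value is only one possible coding. Baseline scores also precede allocation, so leaving zeros out would not by itself bias the comparison.
- **The 2.4 and 1.2 points.** A reader might use these to argue that one point is unimportant for an individual and that an absolute floor should replace the 30% rule. They are differences between group means used for the sample size. No passage supports a 2-point floor, and the 30% rule rests on a cited source not available here.
- **Dilution.** A reader might infer that one-point responders pull the arms together and that a floor would restore the contrast. An illustrative simulation does not bear this out. It used the RMDQ 8 and 10 and NRS 4 and 5 baselines of step 4. Controls fell 25%, the extra benefit was proportional to baseline and averaged 2.4 RMDQ or 1.2 NRS points, and follow-up noise was 0.7 SD. The between-arm difference for the plain rule without zeros, against a rule adding a 2-point floor with zeros as non-responders, was 24.2 against 22.8 percentage points (RMDQ mean 8), 24.1 against 23.6 (RMDQ mean 10), 31.0 against 29.7 (NRS mean 4) and 31.1 against 30.7 (NRS mean 5). Only restriction to baselines of at least 4 widened it.
- **The range of improvement levels.** This helps in part. Thresholds above 50% remove one-point responders at baselines 2 and 3. At baseline 1 one point is 100% and meets any level, and 0 stays undefined.
- **Site.** Clustering of low scores by site is speculation, and the model already has site terms.

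**Conclusion.** The point holds as a limited weakness of a secondary analysis. It is certain from the text that Table 1 sets no severity minimum, that the 30% rule is undefined at 0 and met by one point at 1–3, and that the listed terms omit the baseline score of the scale analysed. How many participants this touches is unknown. The shares in step 4 rest on assumed means and on treating the sample-size SDs as baseline SDs, which the article does not say they are. Everyone enrolled reports low back pain, so a zero is more plausible on the RMDQ than on past-week NRS, but neither is excluded. The 0–5 minimization category concerns worst pain in 24 hours and supports the point only indirectly.

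A reader might go further and infer that the trial's main result is threatened, or that nothing else records how many participants improved. Neither follows. The co-primary mixed models do not use the rule, and a global improvement rating is also collected at weeks 2, 4 and 6 (Secondary outcome measures).

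**What to change.** In Primary data analysis and sample size:

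1. Keep the cited 30% rule as the main responder definition.
2. Add the continuous baseline score of the same scale (RMDQ, or average-pain NRS) as a covariate in the estimating-equation model.
3. State that a baseline of 0 counts as non-response, so that no allocated participant is lost to an undefined ratio.
4. Add a supporting analysis restricted to participants with a baseline of at least 4 on that scale, where one point no longer meets the rule. The restriction uses a pre-allocation value.
5. An absolute-point floor may be shown as a sensitivity analysis, but it should not replace the main definition.

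**Cost.** Plan wording and a little more analysis; all data are already collected. Trial status reports recruitment closed, but Data management and security still describes the database lock as to come, so the rule can be settled before analysis. Responder percentages will be slightly lower. If the share at 0 is the same in both arms, item 3 multiplies the difference by one minus that share; at the assumed 4.7%, 24.2 × 0.953 = 23.1 percentage points. The precision gain from the covariate is likely modest.

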### Statistical methods

The data will be analyzed using an intention-to-treat approach in which participants will be analyzed according to their original treatment allocation. All observed data will be used in the analyses. Data analyses will be performed using SAS/STAT (Release 9.3) (SAS Institute Inc., Cary, NC).

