Two approaches to sensitivity analyses will be used to examine the possible effects of missing data on the results obtained from using all observed data for the co-primary outcome variables. Prior to conducting the sensitivity analyses, baseline variables that are predictive of missing outcomes will be identified with logistic regression models. The first approach will be under the assumption that data are missing at random and will use the Markov chain Monte Carlo method to impute missing values for each of the primary outcome variables based on the final mixed model covariates, the observed outcome variable at baseline and weeks 2, 3, 6, and 12, and the baseline variables predictive of missing data. The resulting datasets for each of 20 imputations will be analyzed with the linear mixed effects models that are fit with all observed data and the results will be combined. The second approach will be under the assumption that data are missing not at random. It will follow the pattern mixture approach described by Carpenter and Kenward [51] by first imputing missing values as described above for the missing at random approach and then for each participant in each treatment group for each imputation. The imputed observation will be decreased by different amounts representing different patterns of responses. The resulting datasets for each pattern will be analyzed and the estimates combined as described above. If results differ between the analysis of the observed data and that based on imputed full datasets under different missingness assumptions, multiple sets of results will be reported.

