#### Secondary data analysis

The continuous secondary outcome variables will be analyzed with linear mixed effects regression as described above, but *p*-values ≤ 0.05 will be used to determine if between group differences are significant. The ordinal categorical variable representing the number of days that participants reported using medications for LBP over the past week will be analyzed over baseline and weeks 2, 3, 6, and 12 with a proportional odds model. Generalized estimating equations using all observed data with a working covariance structure will be used to fit the model.

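### The 30% responder comparison uses unweighted GEE on observed data, so it is less protected against outcome-dependent loss than the primary mixed model, and the planned imputations are not used to check it

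*Protocol article*

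**What the plan says.** All references are to the protocol article, *Statistical methods*, unless stated.

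- The opening paragraph sets a general rule: "All observed data will be used in the analyses".
- *Primary data analysis and sample size* defines the responder as "clinically meaningful improvement of at least 30 % relative to baseline at the week 6 endpoint on the co-primary outcome variables". The method is: "General estimating equations with a working covariance matrix will be used to estimate the differences in proportions between groups at each time point". The covariates are visit, arm, site, two interactions (arm with site and arm with visit) and the factors used for minimization. The same section adds an exploratory look at other improvement levels.
- The missing-data sensitivity analyses in that section address the "possible effects of missing data on the results obtained from using all observed data for the co-primary outcome variables". The missing-at-random approach is to "impute missing values for each of the primary outcome variables based on the final mixed model covariates", other visits' scores and baseline predictors of missingness. The 20 completed datasets are then passed to the linear mixed models; no other use is named.
- *Secondary data analysis* fits medication days with a proportional odds model: "Generalized estimating equations using all observed data with a working covariance structure will be used to fit the model".
- On loss, the sample size paragraph reports pilot missingness at weeks 2 and 4 of 39% and 37% with usual medical care (UMC) alone against 13% and 11% with added chiropractic care. It plans for at most 15% at week 6 in this trial.
- Under *Data collection*, participants may skip secondary measures, and the telephone follow-up of missed assessments seeks only the primary outcomes.

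**The concern.** The co-primary outcomes are analysed by a likelihood-based mixed model, which remains valid when the chance of being missing depends on scores already observed. The responder analysis takes the same two outcomes, dichotomises them, and fits ordinary unweighted GEE, which does not generally have that property. Two summaries of the same data therefore rest on different missingness assumptions, and the one with the stricter assumption has no planned missing-data check.

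The responder share is the form of the result that clinicians and policy makers read most easily. If people who were doing well (or badly) at week 2 or 4 stop responding, the observed week 6 share in that arm shifts, and the responder difference could drift from the mixed-model result for reasons unrelated to treatment. The pilot's loss pattern and the unblinded design make it reasonable to plan for this.

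**Working it through.** **1. The plan's own figure.** 106 evaluable per group per site, inflated for 15% loss: 106 / 0.85 = 124.7, rounded up to 125. This reproduces. Over three sites that is 375 per arm, and 375 × 0.85 ≈ 319 evaluable at week 6.

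**2. When the observed-data GEE is unbiased.** With an independence working matrix and a full group-by-time structure (other covariates set aside), the week 6 estimate in arm g is the responder share among those observed. Let R be week 6 response and S week 2 response. If loss after week 2 depends on arm and S,

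observed share = Σ over s of P(R=1 | S=s, g) × P(S=s | observed, g).

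The true share has P(S=s | g) as the last factor. If loss depends on arm alone, the two factors are equal and there is no bias, however unequal the loss. If loss depends on S, they differ. The GEE conditions on arm, time, site and the minimization variables, but not on S.

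**3. Size, by simulation.** The documents give the NRS standard deviation (2.0), the pilot loss and the 15% target. The other inputs are assumptions: normal NRS, baseline mean 5, week 6 difference 1.0, correlation 0.5 or 0.7 between visits, loss after week 2, log-odds of loss on week 2 non-response of 0 or ±1.4, and an independence matrix. With 1,000,000 per arm, the true responder difference is about 22 points (correlation 0.5) or 27 points (0.7). Bias is in percentage points:

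| Loss, UMC / UMC plus chiropractic | Loss depends on arm only | On earlier response, same direction in both arms | On earlier response, opposite directions |
|---|---|---|---|
| 37% / 11% | 0.0 to +0.1 | −1.4 to +1.5 | −3.0 to +3.2 |
| 15% / 15% | 0.0 | −0.2 to +0.3 | −2.0 to +2.1 |

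Imputing week 6 NRS from baseline and week 2 scores within arm left at most 0.1 point of bias in every cell.

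A second simulation let loss depend on the last observed NRS (about 12,000 per arm, means falling from 5.2 to 3.9, treatment effect −0.8, logistic slope 0.3 to 0.5 per NRS point):

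- Loss of 28% to 41% in UMC and 10% to 13% with chiropractic care: a true difference of 16 to 18 points was underestimated by 2.0 to 3.8 points with an independence matrix and by 0.3 to 0.6 with an exchangeable one.
- Near-balanced loss of 14% to 21%: bias of 0.2 to 0.6 points with an independence matrix.

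A smaller run of the first set-up (20,000 per arm, 37% / 11% loss, same direction) agreed on the working matrix: true 22.0, independence 20.5, exchangeable 21.8 points. Noise in that run is around 0.4 points. Exchangeable was not tried for opposite-direction dependence.

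**4. Against sampling error.** With responder shares of 0.346 and 0.346 + 0.220 = 0.566 and 319 per arm, the standard error of the difference is √[(0.346×0.654 + 0.566×0.434)/319] = 0.0385, or about 3.9 points. A bias of 0.2 to 0.6 points is then 5% to 16% of one standard error, and 2 points is about half. At pilot-like loss (375×0.63 ≈ 236 and 375×0.89 ≈ 334) the standard error is √(0.2263/236 + 0.2456/334) = 0.041, so 3.8 points is about 0.9 of one.

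**The case against.** A reader might infer that the pilot's unequal loss by itself invalidates the GEE, or that GEE needs data missing completely at random. Neither follows. Missingness may depend on any covariate in the model. Group and time-by-group are there, and arm-only loss of 37% against 11% gave essentially no bias. The document reports no loss related to outcome, so the pilot imbalance is a warning sign and not proof.

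Nor does the document suggest that pilot-level loss will recur. The pilot was a separate single-site study of 91 people, with rates for weeks 2 and 4. This trial plans at most 15% loss at week 6, with personal contact and telephone recovery of exactly the outcomes that define response. The independence matrix is also an assumption: the article says only that a working matrix will be used, and that choice may properly sit in an analysis plan not shown. With 15% loss and an exchangeable matrix, the bias may be too small to notice.

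Finally, the article may leave missing-data handling for secondary analyses to that plan. This carries some weight, but the article describes its missing-data work in detail and says where the imputed datasets go: into the mixed models.

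What stands is that the responder analysis makes a stricter assumption than the primary model for the same outcomes, while the material to relax it will already exist. The plan also expects its model covariates may not explain missingness, since it will search for further baseline predictors for the imputation model. None of these enters the GEE.

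**Conclusion.** The point holds as a weakness in a secondary analysis, not as an error in the primary one. The observed-data GEE is sound if loss depends only on covariates in the model, arm included, and in general is not if loss also depends on earlier scores. Under assumed outcome-dependent loss and an independence matrix, bias is about 1.5 to 4 points at pilot-like loss. It is about 0.2 to 0.6 points at near-balanced 14% to 21% loss in the same direction, and up to about 2 points at 15% loss if dependence runs in opposite directions by arm. These sizes rest on the simulated NRS distribution and loss models; RMDQ responders were not simulated.

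Medication days share the weakness and are more exposed, because the item can be skipped and is not recovered by telephone. No size was computed for them. It would be tempting to treat the planned imputations as a remedy there too, but they cover only the primary outcomes.

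**What to change.** Derive responder status, at 30% and across the range of improvement levels, from the 20 NRS and RMDQ imputations already planned. Fit the stated GEE in each and combine the results. Make this the main responder analysis, or at least report it beside the observed-data GEE. The cost is a little programming and slightly different interval widths. Before reuse, correct the imputation model's visit list, which names week 3 where the collection schedule has week 4.

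For medication days a check is a lesser, optional addition. It needs its own imputation, or weights that include earlier post-baseline outcomes. The logistic regressions already planned identify baseline predictors only, and weights built from those would not correct loss that depends on later scores. When tried on the responder contrast at 37% / 11% loss, baseline-only weighting left a bias of −1.6 to −2.8 points, against −1.0 to −2.5 unweighted.

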#### Primary data analysis and sample size

The co-primary outcome variables (RMDQ and the NRS for LBP intensity) will be modeled with linear mixed effects regression over baseline and weeks 2, 4, 6, and 12. We will assume group means are the same at baseline, and include terms in the model for time (as a categorical variable), site, site-by-group, time-by-group, and site-by-time-by-group interactions, and the variables in the minimization algorithm. The covariance structure will be chosen by comparing the maximized log-likelihoods and the Bayesian information criteria for several covariance pattern models against the unstructured covariance. Diagnostics of the conditional predicted values and conditional residuals will be used to assess the assumption of normality and fit for each model.

The main results will be based on the final models for the co-primary outcome variables at the end of the active care phase (6 weeks). If the site-by-time-by-group interaction is significant at the 0.05 level, results will be reported by site. A *p*-value ≤ 0.025 will be used to determine if between group differences are statistically significant.

Because the patient populations at the three sites are different, we calculated a sample size of 106 per group for each site to provide adequate power to detect clinically important differences between groups at each site. The sample size estimates were obtained using a significance level of 0.025 to account for 2 primary outcome variables. The estimates of standard deviation (5.4 for the RMDQ and 2.0 for the NRS for average pain intensity over the past week) come from our pilot study [28]. This provides 80 % power to detect a 2.4 between group difference on the RMDQ and 92 % power to detect a 1.2 difference on the NRS. In the pilot study, there was 13 % and 11 % missing data in the UMC plus chiropractic care group at the week 2 and 4 assessment periods, respectively, but 39 % and 37 % in the UMC alone group. We increased the sample size to 125 per group at each site, assuming we would be able to keep our loss to follow-up at the week 6 endpoint at or below 15 %, due to the implementation of intensive follow-up procedures.

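### The model for at least 30% improvement leaves out the baseline score of the outcome analysed, which forgoes a small amount of precision in a secondary analysis

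*Protocol article*

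**What the plan says.** All references are to the protocol article.

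- **Outcome.** Under Primary data analysis and sample size, the secondary analyses count how many in each group reach a response threshold, described as "clinically meaningful improvement of at least 30 % relative to baseline at the week 6 endpoint on the co-primary outcome variables".
- **Estimand scale.** The estimating equations are meant to "estimate the differences in proportions between groups at each time point". The link function is not named.
- **Model terms.** The same sentence then fixes the covariates: "with terms in the model for time (as a categorical variable), group, site, site-by-group, and time-by-group interactions, and the minimization variables".
- **Minimization variables.** The Allocation section lists them: the algorithm is to "balance group assignment on the factors of sex (M, F), age (18 to <30, 30 to 50), LBP duration". Its one severity factor is the "baseline Numeric Rating Scale (0–5, 6–10) measurement (worse pain in past 24 hours". No RMDQ item is among them.
- **Co-primary outcomes.** Primary outcome measures defines these as follows: "Numeric Rating Scale (NRS) for average pain intensity during the past week and the Roland-Morris Disability Questionnaire (RMDQ". The pain item used for minimization is therefore a different item, and Secondary outcome measures lists it as a separate outcome.
- **Primary model, for contrast.** Each co-primary outcome "will be modeled with linear mixed effects regression over baseline and weeks 2, 4, 6, and 12", with equal group means assumed at baseline. That analysis does use the outcome's own baseline.

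**The concern.** The article names the terms of the responder model, so this is a stated choice and not a detail left to an analysis plan. Read with the Allocation section, the list contains neither baseline RMDQ nor baseline past-week average NRS. The baseline score enters only through the definition of response, and dividing by baseline is not covariate adjustment.

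Whether a participant improves by 30% can still depend on the starting score, through regression to the mean. Where it does, a baseline covariate would explain part of the variation in response. Without it, the difference in proportions is slightly less precise than it could be, and a chance difference in baseline RMDQ between the groups is only partly adjusted for. At stake is a modest amount of precision in the analysis that the protocol links to clinically meaningful improvement. The primary inference is not affected.

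**Working it through.** **No planned figure to reproduce.** The article gives no sample size or power for the responder analysis. Its power statements concern the mean comparisons.

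**Inputs from the article.** RMDQ standard deviation 5.4; between-group RMDQ difference 2.4; 106 per group per site after 15% loss (106/0.85 = 124.7, rounded up to 125); three sites. This gives 3 × 106 = 318 per group at week 6, or about 750 × 0.85 = 638 in all.

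**Assumptions not in the article.** Baseline to week-6 RMDQ correlation 0.3, 0.5 or 0.7; baseline mean 9 or 12; fall in the usual-care group 2 or 4 points; correlation of RMDQ with worst pain 0.3 or 0.5. Scores were rounded to integers and limited to the scale, with baseline at least 1. Response means a week-6 score of at most 0.7 × baseline.

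**Step 1: precision.** For each scenario 400,000 participants were simulated. The residual variance of response was compared between a model with group and pain class and the same model plus baseline RMDQ. Cut in standard error = 1 − √(variance ratio). Equivalent participants = 638 × (1/ratio − 1).

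| Correlation | Variance ratio | Cut in SE | Equivalent participants |
|---|---|---|---|
| 0.3 | 0.916–0.938 | 3.1–4.3% | 42–59 |
| 0.5 | 0.975–0.983 | 0.8–1.3% | 11–16 |
| 0.7 | 0.999–1.000 | about 0% | 0 |

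For example, 1 − √0.916 = 0.043, and 638 × (1/0.916 − 1) = 59. In no scenario did the adjustment raise the variance.

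A second simulation used 318 per group, 1,500 trials per scenario, a logistic model and a standardised difference in proportions. Over correlations 0.3–0.6 it gave variance ratios of 0.937–0.995 for RMDQ. For NRS it gave 0.925–0.998, a cut in standard error of about 0.1–3.8%.

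**Step 2: why the gain fades.** With baseline mean 9 and a 3-point fall in usual care, response in the usual-care group across tertiles of baseline RMDQ was 39%, 56% and 72% at correlation 0.3; 45%, 55% and 63% at 0.5; and flat at 0.7. At the higher correlation, the percent-of-baseline threshold already absorbs the dependence on baseline.

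**Step 3: chance imbalance.** The standard deviation of the group difference in mean baseline RMDQ is 5.4 × √(2/318) = 0.43 points. The slope of response on baseline was about 2.7, 1.5, 0.85 and 0 percentage points per RMDQ point at correlations 0.3, 0.5, 0.6 and 0.7. A one-standard-deviation imbalance therefore moves the difference by:

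- correlation 0.3: 0.43 × 2.7 = 1.2 percentage points
- correlation 0.5: 0.43 × 1.5 = 0.6
- correlation 0.6: 0.43 × 0.85 = 0.4
- correlation 0.7: 0

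The standard error of the difference, with proportions near 50%, is √(2 × 0.25/318) = 0.040, or about 4 percentage points.

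**Step 4: one effect, not two.** The share of variance due to baseline imbalance is (1.2/4.0)² = 9% at correlation 0.3 and (0.6/4.0)² = 2% at 0.5. These match the reductions in Step 1 (6–8% and about 2%). Precision and imbalance must not be counted as separate harms.

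**The case against.** The strongest reply is that nothing here is an error. Allocation is concealed and made by an algorithm, so a responder comparison without baseline RMDQ is not biased in expectation. The model already adjusts for site, sex, age, duration of pain and a pain class. The analysis is secondary and not powered, the primary models use each outcome's baseline, and leaving out one prognostic covariate is common practice. All of this stands, and it limits the point to a refinement.

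The gain may also be nil. The correlation and the baseline mean are assumed, and at a correlation near 0.7 nothing is gained. That stands too, and any statement of size must include this end of the range.

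The adjustment is also not quite free. The article does not state the link function. With an identity link, a continuous covariate can give fitted probabilities outside 0 to 1 or fail to converge, so the estimator may have to change as well. The relation with baseline may not be linear at low RMDQ scores. Both are real but manageable.

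A reader might infer that baseline imbalance carries over in full to the difference in responder percentages. The documents do not support this. The threshold is itself scaled to baseline, and an imbalance of a full point is 1/0.43 = 2.3 standard errors, a chance of about 2%.

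**Conclusion.** The point holds as a minor one. As specified, the responder model has no covariate for the baseline score of the outcome analysed. The expected cost is a standard error for the RMDQ difference in proportions that is larger than it need be by about 3–4% at a baseline to week-6 correlation of 0.3, about 1% at 0.5 and nothing at 0.7. A typical chance imbalance shifts the estimate by 0 to 1.2 percentage points, against a standard error of about 4.

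These figures rest on the article's standard deviation, group difference and week-6 numbers, and on assumed correlations, baseline means and falls in usual care. They apply to the difference in proportions, the scale the protocol names. A smaller standard error for a conditional odds ratio should not be expected. The stronger reading, that the responder result would be biased or the trial's main conclusion weakened, is not supported.

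**What to change.** Before database lock, add the baseline value of the outcome to each responder model: RMDQ in the RMDQ model and past-week average NRS in the NRS model. Fit with a logit link and obtain the difference in proportions at each time point by standardising over the covariates, which avoids the fitting problems of an identity link. State the functional form of the baseline term in advance, and whether it interacts with time.

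No new data are needed. Baseline questionnaires are completed before allocation (Baseline assessment), and the primary measures are required items (Data collection). The cost is a short addition to the analysis specification and slightly more analysis work. Fixing it in advance also avoids a post hoc adjustment if baseline RMDQ turns out to be imbalanced.
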